## 8 PROPOSED ANALYSES

### 8.1 Quantitative data analysis

All analyses will be conducted according to a pre-specified statistical analysis plan. All outcomes will be described with the appropriate descriptive statistics where relevant: mean and SD for continuous outcomes (or medians and interquartile range for skewed data), and counts and percentages for dichotomous and categorical outcomes.

The main effectiveness analysis will be based on the ITT principle. The analysis of the primary outcome will estimate the mean difference (with 95% confidence intervals) in the PFIQ-7 score at 18 months between the self-management and standard care groups using a mixed effects repeated measures model (which assumes incomplete outcome data to be missing at random). The model will incorporate PFIQ-7 scores at baseline, 6, 12 and 18 months, with age (<65/≥ 65) and pessary user type (new/existing) as fixed effects and recruitment centre as a random effect. Missing baseline data will be imputed. The repeated measures model will also estimate mean differences in PFIQ-7 at six and 12 months. Statistical significance will be at the 5% level.

The missing at random assumption for primary outcome data will be assessed further in sensitivity analyses. Treatment effects will be estimated under varying assumptions of data being missing not at random using pattern-mixture models. A complete case analysis will also be conducted.

Secondary outcomes will be analysed using an appropriate generalised linear model (for example binary logistic regression for dichotomous outcomes such as discontinuation with pessary (Y/N), and ordinal logistic regression for ordered categorical outcomes such as women's global impression of improvement (PGI-I). All models will be adjusted for minimisation covariates (age, pessary user type and centre) and baseline score (where applicable).

Given the potential for crossover, we will conduct a secondary analysis of compliers to estimate the effect of receiving the self-management intervention, using complier average causal effect (CACE) estimators. The CACE analysis will take a maximum likelihood approach, which can assume incomplete data to be missing at random, and can be adjusted for covariates. This analysis will provide unbiased effect estimates of receiving the self-management intervention, which will complement the unbiased ITT effect estimates of being offered self-management.

Subgroup analyses will be carried out within the following groups: Age (<65/≥65 years) hysterectomy (Y/N) and type of pessary user (new versus existing). Stricter levels of statistical significance ( $2P < 0.01$ ) will be sought, reflecting the exploratory nature of these analyses. Heterogeneity of treatment effects amongst subgroups will be tested for using the appropriate subgroup by treatment group interactions (Wang 2007).

A single main analysis will be performed at the end of the trial when 18-month follow-up has been completed. The independent DMEC will review confidential interim analyses of accumulating data at its discretion but at least annually.

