## **4. STUDY POPULATION**

### **4.1 Sample Size Calculation**

A sample size of 330 women (165 per group) is required to provide 90% power to detect a difference of 20 points in the PFIQ-7 score at 18 months, assuming a standard deviation of 50, two-sided alpha of 0.05, and 20% loss to follow-up. In order to detect this standardised effect size of 0.4 SDs (20/50 points), 132 women will need to be recruited per group, or 165 per group to allow for dropout. Since the identified centres each see approximately 35 women a month for pessary care, we aim to recruit two to three women per month per centre.

The aim is to recruit a sample size sufficient to detect a 20-point difference in the PFIQ-7 score (the potential range of the PFIQ-7 is 0 to 300), although we acknowledge that an appropriate minimum clinically important difference for PFIQ-7 has not been formally determined. Barber et al. (2005) suggested a minimum clinically important difference (MCID) of 36 points, but it was emphasised that this was based on a small sample and applies only to within-group rather than between-group differences. Therefore, as part of the internal pilot, we will canvass PPI, investigators, and other participating clinicians to gauge the perceived importance of a 20-point difference.

Two recent trials which have used PFIQ-7 in populations of women using pessaries have reported SDs at 12 months and 24 months between 25 and 40 (Weigersma et al., 2014; Panman et al., 2016). These studies however were relatively small, conducted in only a few centres, and neither measured PFIQ-7 at 18 months. Given this uncertainty, a conservative assumption that the SD may be as high as 50 has been made. This will be monitored by examining the variability in the PFIQ-7 score for those women recruited in the internal pilot and we will continue to monitor the aggregated (blinded) SD regularly (every 40 cases using six-month outcome data; and as cases complete at 18 months), with a view to re-estimating the sample size at an appropriate point if required.

A sample size of 330 also provides power for the analysis of secondary outcomes, e.g. we will have more than 90% power (2-sided 5% level of significance) to detect a 20% difference in pessary use continuation rate (assuming at least 50% in the standard care group continue to use a pessary at 18 months).

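### The primary model lists baseline PFIQ-7 with the follow-up scores and not among its adjusters, so its role is unsettled and, read literally, precision is lost

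*Protocol*

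**What the plan says.** Protocol section 8.1 defines the primary estimate as the "mean difference (with 95% confidence intervals) in the PFIQ-7 score at 18 months between the self-management and standard care groups", from a mixed effects repeated measures model "which assumes incomplete outcome data to be missing at random". It then gives the contents of that model: "The model will incorporate PFIQ-7 scores at baseline, 6, 12 and 18 months". The remaining terms follow in the same sentence: "with age (<65/≥ 65) and pessary user type (new/existing) as fixed effects and recruitment centre as a random effect". Baseline PFIQ-7 appears in the list of scores and not in the list of adjusters.

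Three further sentences in the same section bear on the role of baseline:

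- "Missing baseline data will be imputed", stated apart from the handling of missing outcomes.
- "The repeated measures model will also estimate mean differences in PFIQ-7 at six and 12 months". No baseline difference is listed as an estimate.
- In the paragraph on secondary outcomes: "All models will be adjusted for minimisation covariates (age, pessary user type and centre) and baseline score (where applicable").

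Nowhere does the section say whether baseline is a response or a covariate of the primary model, or whether the two groups share a baseline mean.

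**The concern.** The model sentence and the imputation sentence do not fit one model comfortably. If baseline is one of four responses in a likelihood-based model that assumes data missing at random, a woman without a baseline score still contributes her later scores, and imputing her baseline is redundant. If baseline is a covariate, she would drop out of the model without imputation, so the step has a purpose; but then baseline should stand among the adjusters.

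The choice affects the result. With baseline as a response and a free mean for each group at each visit, the 18-month contrast gains essentially nothing from the baseline score. With baseline as a covariate, or as a response with equal group means, chance imbalance at baseline is removed and the standard error falls. Minimisation (section 5.2) balances age group, user type and centre, but not PFIQ-7. Women and centre staff are unmasked (section 10), so it is better that the protocol leaves only one primary estimate open. Appendix D also puts the 4-year analysis in line with the original plan, so the ambiguity carries forward.

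**Working it through.** **Inputs.** From protocol section 4.1: difference 20 points, SD 50, two-sided alpha 0.05, power 90%, 20% loss, 132 per group followed up, 165 per group recruited. The correlation ρ between baseline and 18-month PFIQ-7 is not in the protocol; 0.3, 0.5 and 0.7 are assumptions. Any gain from age group, user type and centre is ignored.

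**1. The plan's own figure.** n per group = 2 × (1.960 + 1.282)² × 50² / 20² = 131.4, rounded up to 132. Then 132 / 0.8 = 165 per group, 330 in total. With 132 per group, SE = 50 × √(2/132) = 6.15, and power = Φ(20/6.15 − 1.960) = 90.1%. The stated size reproduces exactly, and it takes no credit for baseline adjustment.

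**2. Baseline as a response, group means free at every visit.** With complete data, generalised least squares returns the raw difference in 18-month means. SE = 6.15 and power = 90.1% whatever ρ is.

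**3. Baseline as a covariate.** SE = 50 × √(1 − ρ²) × √(2/132).

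| Assumed ρ | SE unadjusted | SE adjusted | Variance reduction (ρ²) | Power unadjusted | Power adjusted |
|---|---|---|---|---|---|
| 0.3 | 6.15 | 5.87 | 9% | 90% | 93% |
| 0.5 | 6.15 | 5.33 | 25% | 90% | 96% |
| 0.7 | 6.15 | 4.40 | 49% | 90% | 99.5% |

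**4. Baseline as a response, group means constrained equal at baseline.** With complete data and a compound-symmetry covariance, the SEs are again 5.87, 5.33 and 4.40. So it is the unconstrained baseline means that remove the adjustment, not the placing of baseline among the responses.

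**5. With dropout.** The same comparison with 165 per group, compound symmetry and an assumed monotone retention of 93%, 87% and 80% at 6, 12 and 18 months:

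| Assumed ρ | SE, free means | SE, equal baseline means | Power, free | Power, equal |
|---|---|---|---|---|
| 0.3 | 6.07 | 5.84 | 90.9% | 92.8% |
| 0.5 | 5.95 | 5.28 | 91.9% | 96.6% |
| 0.7 | 5.80 | 4.33 | 93.2% | 99.6% |

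The free-means model recovers a little through the missing data, but most of the gap remains.

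**6. How far the two estimates can differ.** With equal SDs at both visits (section 3.1 also uses 50 for baseline), the adjusted and raw estimates differ by ρ times the observed baseline difference. A chance difference of one standard error at 132 per group (6.15 points) would separate them by 0.3 × 6.15 = 1.8, 0.5 × 6.15 = 3.1 or 0.7 × 6.15 = 4.3 points.

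**The case against.** The best defence is that the protocol never calls the primary estimate unadjusted. The verb *incorporate* can cover a covariate as well as a response. Imputing missing baselines separately from missing outcomes suggests a covariate. The listed contrasts are at 6, 12 and 18 months only. The sentence on adjusting all models for baseline score is worded widely enough to take in the primary model. Model detail may also sit in the statistical analysis plan, to which section 8.1 refers and which is not at hand.

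Much of this stands. A reader might infer that the primary estimate is certainly unadjusted for baseline; the text does not support that, because a response model with equal baseline means is fully adjusted and the covariate reading is open. A reader might infer that the imputation makes no sense; it is natural under one reading and merely redundant under the other. A reader might infer bias or a shortfall in power; neither follows, since randomisation keeps the raw contrast unbiased and section 4.1 sized the trial without adjustment ("A sample size of 330 women (165 per group) is required to provide 90% power to detect a difference of 20 points").

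The defence does not settle the role of baseline. The sentence on all models stands in the secondary-outcome paragraph and repeats covariates already given for the primary model, which suggests that it was written for the secondary outcomes. Nor is this only detail left for later: the protocol itself fixes the scores, the adjusters and the imputation, and these do not sit together in one model without explanation.

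**Conclusion.** The point holds as a tension in the stated primary model with a costless improvement, not as an error that endangers the trial. Followed literally with free group means at baseline, the 18-month difference is essentially the raw one. Its SE is then 5%, 15% or 40% larger than the adjusted SE at ρ = 0.3, 0.5 or 0.7 (1/√(1 − ρ²) = 1.05, 1.15, 1.40). These sizes rest on the assumed ρ, on SD 50, on complete data for 132 per group, and on the literal reading. If the intended model has baseline as a covariate, or equal baseline means, no precision is lost and only the wording needs repair. Unbiasedness and the planned 90% power hold under every reading.

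**What to change.** State one of these in section 8.1 as the primary model, and match the statistical analysis plan to it:

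1. Responses at 6, 12 and 18 months; baseline PFIQ-7 as a covariate; treatment-by-time, age group and user type as fixed effects; centre and participant as random effects. Keep the imputation of missing baselines.
2. All four visits as responses, with the baseline means of the two groups constrained equal, and the remaining terms as above. Delete the imputation sentence.

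With complete data the two give the same precision, so either will do; what matters is that one is named. The 4-year analysis should then follow the same choice. The cost is a wording change in the protocol and the analysis plan. Baseline PFIQ-7 is already collected, and neither the sample size nor trial conduct changes.

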## **8.2 Process Evaluation Data Analysis**

Each data source will be analysed individually in the first instance to reach separate conclusions and findings then synthesised across data sources. All qualitative data sources will be transcribed verbatim and entered into Nvivo 11 for data management. Ten percent of transcripts within each data source will be coded independently by two analysts to assess for inter-rater reliability. All of the analysis

described below will be undertaken by the process evaluation subgroup of grant-holders. Analysis will not be shared with the wider grant-holding group until the main trial findings are revealed.

All **qualitative data** (audio-recordings of recruitment sessions; interviews with randomised women, women who declined randomisation and with healthcare professionals; and the open question within the questionnaire) will be analysed using the Framework Approach (Spencer et al., 2014) except for the audio-recordings of the self-management teaching appointments and the self-management follow up phone calls. Framework analysis will move through stages of data management, descriptive analysis and finally onto interpretive and explanatory analysis. For **each individual dataset** the recommended Framework stages will be followed:

#### Data Management

- *Familiarisation:* by listening to audio-recordings and reading transcribed data the analyst will familiarise themselves with the individual data set.
- *Construction of an initial thematic framework:* The thematic framework for each dataset will be developed from: the research questions; the data collection tools (e.g. interview schedules); themes that have arisen iteratively from the familiarisation process; discussion with co-applicants; and PPI consultation.
- *Indexing and sorting:* The thematic framework will be applied to all data within each dataset. The thematic framework will continue to iteratively evolve as indexing and sorting occurs.
- *Reviewing data extracts:* Involving PPI representatives and the qualitative analysis team the thematic framework will be reviewed and alternative ways of indexing the data considered.
- *Data summary and display:* Using framework tables (generated within Nvivo) each main theme will be displayed in a table(s). Some tables will have arisen from iterative analysis and others will arise from the purposes of the study. Specifically, there will be at least one table from each of the relevant data sources that focusses on: maximising recruitment, assessment of eligible but non-randomised women; experience/acceptability; adherence to allocated trial group; fidelity to intervention delivery; and contextual factors that influence effectiveness of standard pessary care/ self-management. For example, for maximising recruitment there will be a table each from the analysis of: recruitment sessions in the internal pilot study; interviews with randomised women; interviews with women who decline randomisation and interviews with recruiting healthcare professionals.

#### Abstraction and Interpretation

Abstraction and interpretation will occur first for each individual dataset and then the datasets will be combined.

- *Description (developing categories and mapping linkage):* Categories, within each data set, will be developed by reviewing tables and analytic memos, and by comparing and contrasting tables with a view to moving analysis onto a more interpretive level. Linkages will be made through exploration of how tables and the themes within them connect to one another. This process will be repeated for each of the purposes of the process evaluation to develop one overarching matrix for each purpose (O’Cathain et al., 2010) e.g. bring the tables together that focus on maximising recruitment into one matrix.
- *Explanation* will aim to bring the data together to interpret why the data have come together in the specific way that is presented. Analysis at this point will particularly focus on comparisons between standard care and self-management in ways that facilitate drawing overall conclusions about why self-management may or may not be effective, and which components of self-management are most important for future implementation.

**Audio-recording of self-management teaching appointments and self-management follow up phone calls (fidelity)** will be analysed by developing a structured analytic grid using the intervention protocols and the theory underlying the protocols. The grid will assess for key features within the teaching appointments and phone calls, for example does the healthcare professional teaching self-management offer the woman an opportunity to practice taking the pessary out and replacing it. The grid will contain explicit guidance as to what codes have to be applied in what circumstances. Coded data will then be subject to quantitative descriptive and interpretive analysis.

**Analysis of secondary outcome self-report questionnaires to randomised women (experience/acceptability, adherence, contextual factors)** will be analysed in line with the quantitative analysis described in section 8.1.

### **8.3 Economic Analysis**

#### *Cost-Effectiveness Analysis*

The primary analysis will be undertaken at 18 months from an NHS perspective. All costs and outcomes beyond one year will be discounted at 3.5% (NICE, 2013). A broader perspective including women’s personal expenditures will be included in a sensitivity analysis. Incremental cost-effectiveness ratios (ICERS) will be computed by comparing the costs and outcomes of the self-

management and standard care trial groups. The difference in effectiveness will be expressed in terms of the change in score on the primary outcome measure PFIQ-7 (cost-effectiveness analysis). The difference in utility between the two groups will be expressed in terms of QALYs calculated using the UK value set for patient-reported EQ-5D-5L data (Devlin et al., 2017).

This will be used in a Cost Utility Analysis to calculate the incremental cost per QALY gained.

### *Longer term Decision Modelling*

To examine the costs and outcomes of self-management compared to standard care beyond the trial period we will undertake decision modelling. This will involve extrapolating data we have from the trial period and adding additional data from the literature and routine data sources. A five-year time frame would be used and the care pathway over this period will be mapped out. We will incorporate data on: number of women who would want to self-manage, continued pessary use, continuation rates for self-management, complications and adverse events, conversion to surgery rates for both self-management and standard care, health outcomes (prolapse and general quality of life outcomes), expenditure attending follow-up appointments in both groups, expenditure on replacement pessaries in both groups (type-dependent), other (potentially rare) outcomes of interest that we would unlikely to see during the 18 month trial period (e.g. fistula).

## **9 ORGANISATION - Trial coordination**

### **9.1 Sponsor**

Glasgow Caledonian University will now act as study sponsor and their finance department will be responsible for the financial management of the grant including agreeing contracts with collaborating institutions and submitting financial reports to HTA as required.

### **9.2 Clinical Trials Unit**

The trial is supported by The Centre for Healthcare Randomised Trials (CHaRT Aberdeen). CHaRT has considerable experience with similar trials in this area and will develop the data management system, a remote randomisation system and will be responsible for ensuring the reliability of data at data-lock to ensure compliance with the Research Governance Framework and Good Clinical Practice.

### **9.3 Study offices**

From June 2022, there will only be one TOPSY study office. This will be based at Glasgow Caledonian University.

### **9.4 Trial centres**

#### ***Local Principal Investigator***

Each collaborating centre will identify a lead clinician (local Principal Investigator) who will be the point of contact for that centre. The responsibilities of this person will be to:

- establish the trial locally (for example, by getting agreement from clinical colleagues; facilitate local regulatory approvals; identify, appoint, train and supervise staff who are recruiting at the site; and inform all relevant local staff about the trial)
- take responsibility for clinical aspects of the study locally (for example if any particular concerns occur relating to wellbeing of a participant)
- notify the TOPSY Study Glasgow Office of any unexpected clinical events which might be related to trial participation
- provide support, training and supervision for the 'local TOPSY research team'
- reporting any adverse events or serious adverse events
- represent the centre at any collaborators' meetings.

#### ***Intervention Healthcare Professional (HCP)***

Each collaborating centre will appoint a local Intervention HCP as part of the local TOPSY research team who will be trained on the self-management intervention and who will keep regular contact with the local PI, with notification of any problem or unexpected development.

Each centre will have a centre initiation visit to ensure all study processes are in place before recruitment commences. The TOPSY Study Glasgow Office will set-up regular centre 'forums' for all centres to 'phone in' and discuss any problems experienced and share learning. Updates will be provided via quarterly newsletters. Centres having specific problems with recruitment and/or retention will be offered additional support either remotely or by an additional centre visit.

## **9.5 TSC and DMEC**

An independent Trial Steering Committee (TSC) will review the study on behalf of the sponsor and the funder. The TSC will include an independent chair, clinicians with expertise in prolapse/pessary management, a member of the public and a member of the PMG; a representative from the sponsor and the funder will be invited to meetings of the TSC and minutes will be copied to the funder. The TSC will meet at least annually to supervise trial conduct to ensure the principles of Good Clinical Practice and relevant regulations are adhered to and will advise on the stop/go criteria specified in section 3.1.

A separate and independent Data Monitoring and Ethics Committee (DMEC) will be convened. This Committee will be independent of the trial organisers and the TSC. It is anticipated the members will meet once to agree terms of reference and then annually (or more frequently if required) to monitor accumulating data and oversee safety issues.

During the period of recruitment to the trial, the DMEC will review a report on accumulating safety data, together with any other analyses that the committee may request, at each meeting, and any serious adverse events reported to the DMEC as detailed in Section 10.1. In the light of this report, the DMEC will advise the Trial Steering Committee if, in its view, the trial should continue as planned, or stop early due to clear harm or benefit of a treatment, or external evidence; it may also make recommendations as to other amendments to the trial protocol based on this report.

The Chair and the other independent members of the TSC and DMEC are to be appointed after confirmation by the HTA.

